## Abstract

**Background:**

The development of liver cirrhosis is usually an asymptomatic process until late stages when complications occur. The potential reversibility of the disease is dependent on early diagnosis of liver fibrosis and timely targeted treatment. Recently, the use of non-invasive tools has been suggested for screening of liver fibrosis, especially in subjects with risk factors for chronic liver disease. Nevertheless, large population-based studies with cost-effectiveness analyses are still lacking to support the widespread use of such tools. The aim of this study is to investigate whether non-invasive liver stiffness measurement in the general population is useful to identify subjects with asymptomatic, advanced chronic liver disease.

**Methods:**

This study aims to include 30,000 subjects from eight European countries. Subjects from the general population aged ≥ 40 years without known liver disease will be invited to participate in the study either through phone calls/letters or through their primary care center. In the first study visit, subjects will undergo bloodwork as well as hepatic fat quantification and liver stiffness measurement (LSM) by vibration-controlled transient elastography. If LSM is ≥ 8 kPa and/or if ALT levels are ≥1.5 x upper limit of normal, subjects will be referred to hospital for further evaluation and consideration of liver biopsy. The primary outcome is the percentage of subjects with LSM ≥ 8kPa. In addition, a health economic evaluation will be performed to assess the cost-effectiveness and budget impact of such an intervention. The project is funded by the European Commission H2020 program.

**Discussion:**

This study comes at an especially important time, as the burden of chronic liver diseases is expected to increase in the coming years. There is consequently an urgent need to change our current approach, from diagnosing the disease late when the impact of interventions may be limited to diagnosing the disease earlier, when the patient is asymptomatic and free of complications, and the disease potentially reversible. Ultimately, the LiverScreen study will serve as a basis from which diagnostic pathways can be developed and adapted to the specific socio-economic and healthcare conditions in each country.

**Trial registration:**

This study is registered on Clinicaltrials.gov (NCT03789825).

**Supplementary Information:**

The online version contains supplementary material available at 10.1186/s12889-022-13724-6.

## Background

Liver cirrhosis is the end stage of chronic liver diseases and is a major cause of morbidity and mortality worldwide. According to data from the Global Burden of Disease Study, cirrhosis is the 11^th^ cause of death globally and the 7^th^ and 12^th^ leading cause of disability-associated life years (DALY) in people aged 50-74 years and 25-49 years respectively [1]. It is also the second cause of years of working life lost in Europe [2]. The main etiologies of cirrhosis are hepatitis B and C virus infection, increased alcohol consumption and non-alcoholic fatty liver disease (NAFLD), the latter of which is often associated with obesity and type 2 diabetes mellitus [3].

The development of cirrhosis, regardless of its cause, usually occurs very slowly over 2-3 decades, a period during which collagen relentlessly deposits within the liver until the normal liver architecture is disrupted and portal hypertension develops. In general, patients are not diagnosed during this period because fibrosis deposition is an asymptomatic process [3]. As such, most cases of cirrhosis are diagnosed when patients develop complications related to portal hypertension, liver failure or liver cancer. No global strategy exists for the early detection of cirrhosis before such decompensation or cancer occurs. Nevertheless, the main factor predicting long-term outcomes in patients with chronic liver disease is the existence of liver fibrosis [4, 5], which highlights the importance of identifying the disease early. Although some studies have demonstrated the potential reversibility of liver fibrosis after treating the etiology, the actual effectiveness of treatments decrease in late stages compared to early stages of fibrosis [6]. Emphasis should therefore be put on early diagnosis of disease to maximize its potential reversibility.

Standard liver biochemical tests such as serum aminotransferases, or liver ultrasound, are not accurate methods to detect fibrosis [3]. In recent years, several non-invasive methods assessing the presence and severity of liver fibrosis have been developed. These methods rely either on a blood test or on liver stiffness measurement (LSM), using vibration-controlled transient elastography (VCTE) (FibroScan®, Echosens, Paris), which is the most used and validated non-invasive tool for staging chronic liver diseases [7–10]. VCTE is a point-of-care technique that can be performed by nurses after a short training period, and consequently a large number of people can be assessed [11]. While VCTE is available in many liver centers, it is mostly not available in primary care settings where the early detection of liver fibrosis should in fact take place. This technique is particularly suited for the early detection of chronic liver disease either in the general or in high-risk populations, particularly in patients with obesity, diabetes or increased alcohol consumption [9]. Moreover, previous data suggest that the strategy of liver fibrosis screening using TE may be cost-effective [12] but require further validation.

### Study Rationale and Hypothesis

Different recommendations have been made by the scientific community to assess liver fibrosis, especially in at-risk populations, using non-invasive tools [10, 13, 14]. However, these recommendations are based on previous studies that either had insufficient sample size, did not systematically confirm the diagnosis with a liver biopsy, or were not specifically designed to assess the cost-effective strategy in terms of health outcomes and treatment costs in either general or at-risk population [15]. Therefore, we hypothesize that a screening program using a non-invasive method for the diagnosis of liver fibrosis may be useful in detecting asymptomatic subjects with advanced liver fibrosis. This early detection of disease would allow the implementation of treatment with the aim of halting progression or even favoring regression of fibrosis, thus preventing the development of hard clinical outcomes related to the liver disease, such as liver cirrhosis, liver cancer, or liver-related death.

### Study Aim

This is a population-based study aimed at investigating whether liver stiffness measurement using transient elastography is useful to identify subjects with asymptomatic significant chronic liver disease in the general population.

### Study design

This study is a single group screening study. It has been registered retrospectively on Clinicaltrials.gov (NCT03789825) the 14^th^ of November 2018. First patient included was in May 2018.

The present population-based study will include 30,000 subjects in eight European countries (Fig. 1). Eligible participants will be invited to attend at their primary care centre or at a research facility where a nurse will perform visit 1. This visit will include a detailed interview, physical examination, questionnaires related to alcohol consumption, quality of life and health status assessment, venipuncture for liver biochemical tests assessment and biobanking, and VCTE to assess LSM and controlled attenuation parameter (CAP). If participants show a LSM ≥ 8 kPa, unreliable or failed VCTE measurement [16] and/or increased ALT levels (ALT ≥ 1.5 x upper limit of normal value), they will be referred to second visit in a Liver Unit at the academic center for further evaluation (visit 2). Otherwise, the study finishes after completion of visit 1 (Fig. 2). Visit 2 will be completed by hepatologists within the 3 months following visit 1, according to a standardized work-up for liver disease diagnosis and evaluation. Visit 2 will include evaluation of the participant’s medical history, physical examination with complete liver tests, FibroScan examination and abdominal ultrasound. The FibroScan examination at visit 2 will be performed with both probes (M and XL). Afterwards, a liver biopsy will be offered to the patient for diagnosis and staging of liver disease when LSM is above 8 kPa or if chronic liver disease is suspected, as per standard of care.

**Fig. 1 Fig1:**
[figure not shown]
Countries included in the LiverScreen project

**Fig. 2 Fig2:**
[figure not shown]
Study flowchart. LSM, liver stiffness measurement; ULN, upper limit of normal

Following diagnosis and staging at the corresponding university hospital, all patients will be offered standard of care treatment and follow-up. Patients with NAFLD will be offered a lifestyle modification program consisting of diet and exercise targeting weight loss of 10% and controlling risk factors of liver disease progression. Each center will offer the specific program according to its own protocol. Patients with NAFLD participating in the present study can still be included in other studies related to NAFLD that evaluate pharmacological treatments. Such treatment received in the context of clinical trial or other pharmacological interventions will be recorded. Patients with high alcohol consumption will be offered psychological assessment and counseling to stop drinking or, at least, reduce harmful alcohol use. Finally, patients diagnosed with chronic liver disease from other etiologies (autoimmune disease, viral hepatitis, Wilson disease, etc.), will be treated according to guidelines [13, 17–20]. All participants with LSM by VCTE < 8 kPa and ALT levels <1.5 ULN who present risk factors for chronic liver diseases such as increased alcohol consumption or obesity will be counseled on lifestyle modifications by their primary care physician for management of such risk factors.

Participants that fail to attend to visit 2 will be contacted by their primary care physician or nurse and referred again to the second visit. Participants will be asked to consent to be contacted in the future for a re-evaluation at 5 and 10 years after visit 1. Information regarding liver-related clinical outcomes (presence of cirrhosis, decompensated cirrhosis, liver cancer and liver-related death), cardiovascular events, and all causes of death will be collected. Patient assessment will be performed through clinical records (via health care registries or health insurance systems) or telephone contact. No further visits will be performed. These clinical outcomes will be used to inform the cost-effectiveness analysis of the liver fibrosis screening program.

#### Primary outcome measure

Percentage of subjects with LSM by VCTE ≥ 8 kPa at any visit, either with the M or XL probe, in the general population.

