#### Secondary outcome measures

Percentage of subjects with LSM by VCTE ≥ 8 kPa in the subgroup of patients with risk factors for chronic liver diseases at visit 1 and/or 2.Comparison of liver fibrosis diagnosis accuracy between VCTE and fibrosis scores (including NAFLD fibrosis score, FIB-4, Forns index and APRI score) in the general population and in the subgroup of patients with risk factors for chronic liver disease, at visit 1 and 2.Comparison of liver fibrosis diagnosis accuracy between VCTE, fibrosis scores and liver biopsy in the general population and in the subgroup of patients with risk factors for chronic liver diseases, in patients with a liver biopsy available at visit 2.Percentage of subjects with controlled attenuation parameter (CAP) ≥ 250 dB/m, either with M or XL probe, in the general population and in the subgroup of patients with risk factors for chronic liver diseases at visit 1 and/or 2.Comparison of liver steatosis diagnosis accuracy between CAP and steatosis scores (including fatty liver index (FLI), hepatic steatosis index (HSI), lipid accumulation product (LAP), index of NASH (ION) and NAFLD-liver fat score (NAFLD-LFS)) in the general population and in the subgroup of patients with risk factors for chronic liver diseases at visit 1 and 2.Comparison of liver steatosis diagnosis accuracy between CAP, steatosis scores (including FLI, HSI, LAP, ION and NAFLD-LFS) and liver biopsy in the general population and in the subgroup of patients with risk factors for chronic liver diseases, in patients with liver biopsy available at visit 2.Comparison of liver steatosis diagnosis accuracy between CAP and abdominal ultrasound in the general population and in the subgroup of patients with risk factors for chronic liver diseases, in patients with abdominal ultrasound available at visit 2.Comparison of values obtained with M and XL probes in the assessment of LSM and CAP using VCTE at visit 2.Cost-effectiveness and budgetary impact of a liver fibrosis screening program for liver fibrosis detection in the general population and in the subpopulation with risk factors for chronic liver diseases. Direct and indirect cost savings of early detection of liver fibrosis in subjects with risk factors for chronic liver diseases.Percentage of measurement failure during VCTE examination at visit 1 and 2.Percentage of patients with procedure-related adverse events (adverse events related to VCTE and/or liver biopsy) and serious adverse events during the duration of the study.Detection of common genetic variants, single nucleotide polymorphisms (SNPs), in patients with and without significant hepatic fibrosis or chronic liver diseases, including genome-wide association studies (GWAS) and whole-genome sequencing (WGS) in blood samples.Incidence of cirrhosis, liver cancer, and liver-related death and all-cause of mortality in patients with significant fibrosis and/or severe steatosis after 5 and 10 years from the first evaluation.Incidence of cardiovascular events in patients with significant fibrosis and/or severe steatosis after 5 and 10 years from the first evaluation.

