**BIOBANK**		
Blood samples: plasma, serum, DNA.	**X**	
**VC TRANSIENT ELASTOGRAPHY**	**X**	**X**
**ABDOMINAL ULTRASOUND**		**X**
**LIVER BIOPSY**		**X**
**AE assessment**	**X**	**X**

*AE* adverse event, *AP* alkaline phosphatase, *α1AT* α1-antitrypsin, *CRP* C-reactive protein, *HBV* hepatitis B virus, *HCV* hepatitis C virus, *TSH* thyroid stimulating hormone

**Liver fibrosis** will be estimated by three different methods: LSM, liver fibrosis scores and liver biopsy.LSM will be performed in all patients using VCTE. LSM will be performed with M or XL probe following the Automatic Probe Selection tool available on the Fibroscan®. LSM will be repeated at visit 2 in those patients referred to the university hospital. Significant liver fibrosis by VCTE will be defined by a LSM ≥ 8.0 kPa with either M or XL probe.Fibrosis scores/serum biomarkers: Four different established liver fibrosis scores using different blood tests will be determined at visit 1: NAFLD fibrosis score (NFS), Forns Index, Fibrosis-4 (FIB-4) and AST to Platelet Ratio Index (APRI). Significant liver fibrosis will be defined when the values of the different scores are above the following cut-offs, according to literature [8, 10]: NFS ≥ 0.676, Forns index ≥ 6.9, FIB-4 ≥ 2.67, APRI ≥ 1.50.Liver biopsy. In patients with a liver biopsy available, liver fibrosis will be assessed and defined according to SAF/NASH CRN Score [21] and analyzed by two central readers. Discrepancies between two readers will be re-assessed and discussed until consensus.

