### Statistical analyses

Categorical parameters will be presented by means of frequencies (%). Continuous parameters will be summarized by mean ± standard deviation or median and interquartile range, where appropriate. All patients having a VCTE examination with valid measurements [8] will be included in the analysis population. Subjects excluded from the analysis will be compared to those having a VCTE examination with valid measurements using the Chi squared test and t-test for categorical or continuous characteristics respectively. Prevalence and its 95% confidence intervals (95%CI) of LSM ≥ 8 kPa will be computed overall (primary endpoint) and in the subgroup of patients with risk factors. Analogously, prevalence of CAP ≥ 250 dB/m and its 95%CI will be computed, overall and among patients with risk factors. Concordance between variables (LSM, fibrosis scores, CAP, steatosis scores, liver biopsy) will be computed. Scatter plots and Pearson’ r linear correlation coefficients will be used to explore the relationship between continuous variables, including LSM and fibrosis scores values. Receiver operating characteristic (ROC) curves, using LSM ≥ 8 kPa as the gold standard for fibrosis, will be computed for the different continuous fibrosis scores. Sensitivity, specificity, predictive values and likelihood ratios will be performed using LSM ≥ 8 kPa as the gold standard for fibrosis for different fibrosis categorized scores. Comparison of values obtained with M and XL probes in the assessment of LSM and CAP will be performed both, using the continuous forms of the variables with t tests (or non-parametric tests in the case these variables violate the necessary assumptions), and using the categorical variables using the 8 kPa and 250 dB/m^2^ cut-offs with Chi squared test. In addition, multivariate linear regression models and multivariate logistic regression models will be computed with LSM (or CAP) as the dependent variable (continuous for linear model and categorical for logistic mode) to assess the effect of the M or XL and potential interaction with the probe size. The relative frequency of adverse events to the study procedures will be reported in percent.

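### The primary outcome counts a positive LSM at any visit with either probe, but only referred subjects are re-measured, so the general-population prevalence is unequally ascertained

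*Protocol article*

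**What the plan says.** The section Primary outcome measure defines the endpoint as the percentage of subjects with "LSM by VCTE ≥ 8 kPa at any visit, either with the M or XL probe", and labels it as a figure for the general population.

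The number of readings behind that definition differs between subjects:

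- **Visit 1, everyone.** Measurements and investigation procedures states that "LSM will be performed with M or XL probe following the Automatic Probe Selection tool available on the Fibroscan", so there is one examination on one probe.
- **Visit 2, referred subjects only.** The same section says "LSM will be repeated at visit 2 in those patients referred to the university hospital". Study design adds that this examination uses both the M and the XL probe, and that the study ends after visit 1 for everyone not referred.
- **Who is referred.** Study design gives the rule: "If participants show a LSM ≥ 8 kPa, unreliable or failed VCTE measurement [16] and/or increased ALT levels", the ALT threshold being 1.5 times the upper limit of normal.

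Statistical analyses plans one overall prevalence with a 95% CI and adds no visit or probe rule. It sets the analysis population as follows: "All patients having a VCTE examination with valid measurements [8] will be included in the analysis population". The visit is not named. Secondary outcome measures scores steatosis in the same way: "controlled attenuation parameter (CAP) ≥ 250 dB/m, either with M or XL probe", at visit 1 and/or visit 2.

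**The concern.** A percentage described as holding in the general population should rest on the same opportunity to be positive for every subject. Here the opportunity depends on ALT, on whether the visit 1 examination succeeded, and on attendance at visit 2. The stated rule takes the highest available reading, and some subjects have more readings than others.

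The resulting figure is neither the prevalence from one screening examination nor the prevalence that would follow if everyone had three readings. It lies between the two, at a point set by referral and attendance. The protocol expects some non-attendance, since Study design provides for re-contacting people who miss visit 2. This is the study's headline estimate, and prevalence is also named among the quantities for which the economic model will be calibrated by country.

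**Working it through.** **Inputs from the Protocol article.** Planning prevalence p = 3% and N = 30,000 (Sample size calculation); the referral and measurement rules above. The plan gives no figure for the effect of repeat readings, so there is none to reproduce. The calculated 28,887 comes without a stated precision or alternative, cannot be re-derived from its own inputs, and is not used below.

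**Step 1: which subjects can change status.**

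| Visit 1 result | Readings that can count | Effect of the any-visit, either-probe rule |
|---|---|---|
| Valid LSM < 8 kPa, ALT not raised | 1 | none |
| Valid LSM ≥ 8 kPa | 3 if attending | none: already positive |
| Valid LSM < 8 kPa, ALT-referred, attends visit 2 | 3 | can only become positive |
| Failed or unreliable, attends visit 2 | 2 | positive if the higher of two is ≥ 8 kPa |

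In the first three rows no positive can be lost, so the direction needs no assumption.

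**Step 2: yardstick.** The 95% CI half-width at the planning values is 1.96 × √(0.03 × 0.97 / 30,000) = 0.00193, or 0.19 percentage points (pp).

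**Step 3: added positives from ALT-referred subjects.** The increase is

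Δ = (share of all subjects ALT-referred with visit 1 LSM < 8 kPa) × (attendance) × P(M or XL ≥ 8 kPa at visit 2).

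None of these three terms is in the documents. The assumptions are log-normal LSM with visit 1 prevalence fixed at 3%, ICC 0.80-0.95, independent measurement error for each reading, ALT referral twice as likely when true stiffness is above the cut-off, and full attendance. Simulation gives:

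| ALT-referred | Added prevalence (pp) |
|---|---|
| 1-2% | 0.02-0.07 |
| 3% | 0.05-0.09 |
| 5% | 0.09-0.16 |
| 10% | 0.17-0.31 |

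As a plausibility check, at 5% referral the conversion rate is about 0.09/5 = 1.8% to 0.16/5 = 3.2% of those referred on ALT. Attendance scales the result directly: at an assumed 80%, the 5% row becomes 0.8 × 0.09 = 0.07 to 0.8 × 0.16 = 0.13 pp.

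**Step 4: sensitivity to the link between ALT and stiffness.** If doubled ALT referral applies to the stiffest 20% of subjects, not only to those above the cut-off, the upper end at 10% referral is 0.46 pp. A separate model with lower repeatability (ICC 0.66-0.84), 1-5% ALT-referred and an ALT-stiffness correlation of 0-0.4 gives 0.025-0.50 pp.

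**Step 5: failed or unreliable examinations.** In that second model, with an assumed 3% of subjects in this group, 4.4-5.3% are positive on the higher of two readings, against about 3.0% on one. The contribution is 0.03 × (4.4 − 3.0) = 0.04 pp to 0.03 × (5.3 − 3.0) = 0.07 pp. With Step 4 of the same model, 3.00% becomes 3.06-3.56% overall.

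**Step 6: comparison.** In the Step 3 model the shift exceeds 0.19 pp only at 10% ALT-referred: for two of the three ICC values tried (0.80, 0.90, 0.95) at full attendance, and for one at 80%.

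**The case against.** The strongest defence is that the rule is explicit, stated in advance and suited to the aim. Study Aim asks whether LSM is useful for identifying people with disease, and someone detected at either step of a two-step pathway is a genuine yield of the programme. That stands as a reason to report the any-visit figure. It does not make that figure a general-population prevalence, which is how the outcome is labelled.

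The size is also open to challenge. With 1-5% ALT-referred, the Step 3 shift stays below the CI half-width. Treating the M and XL readings of one visit as independent tends to overstate the gain, although a systematic difference between probes could act the other way. This stands, and it limits the severity.

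A late change of primary outcome has its own cost. Study Status reports 14,539 subjects enrolled by March 2022, about half of 30,000, and registration was already retrospective. This is a fair reason to offer an alternative to redefinition.

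Three stronger readings are tempting, and the documents do not support them:

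- *All referred subjects get three chances to become positive.* Those referred for LSM ≥ 8 kPa are already counted, and those with a failed or unreliable visit 1 have two valid chances at most.
- *Visit 1 false positives that stay positive show inflation by this rule.* They would equally stay positive under a visit 1-only outcome, so a lower visit 2-confirmed percentage is no evidence against the any-visit rule.
- *The rule invalidates comparisons between countries.* No between-country comparison of prevalence is a listed outcome or analysis. The economic model is only to be calibrated by country, and the article gives no referral or attendance rates by site.

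**Conclusion.** The point holds as one of unequal ascertainment, and it should be fixed. The protocol's own rules give extra chances of a positive result to ALT-referred attenders with visit 1 LSM < 8 kPa, and score failed or unreliable visit 1 subjects on the higher of two readings. Nothing in the article corrects for this. Among subjects with a valid visit 1 reading the figure can only equal or exceed the single-examination prevalence. Upward is meant relative to that benchmark only: in the second model, giving everyone three readings would yield 5.4-6.7%.

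The size cannot be settled from the documents. Under the stated assumptions (1-10% ALT-referred, ICC 0.80-0.95, full attendance) the ALT-referred group adds about 0.02-0.3 pp to 3.0%, and up to about 0.5 pp if ALT and stiffness are more broadly linked. Against a half-width of 0.19 pp the effect is often within sampling error, so a reader should not infer that the primary result is unusable. But it is systematic, and a larger N leaves it unchanged while narrowing the interval around it.

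**What to change.** Base the general-population prevalence on one reading per subject: the visit 1 LSM on the automatically selected probe. Use a visit 2 reading only where visit 1 failed or was unreliable, and then only one, on the automatically selected probe. Name the visit in the definition of the analysis population accordingly.

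Report the any-visit, either-probe percentage separately as programme yield, and the percentage of visit 1 positives confirmed at visit 2 as a secondary outcome. Apply the same one-reading rule to CAP ≥ 250 dB/m and to the risk-factor subgroup.

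If the sponsor prefers not to change the primary outcome mid-enrolment, the visit 1 one-reading estimate should be pre-specified as a named analysis and reported beside it.

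The cost is a documented amendment and a slightly lower headline figure. No new measurements are needed and N does not change.
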